#### ○ Early termination of the clinical trial (for a participant)

1. During the clinical trial, if symptoms improve and, based on both the participant's personal request and the judgement of the clinical trial physicians, it is determined that no further treatment is necessary, the clinical trial may be **terminated early** for that participant.
2. Participants whose clinical trial participation is terminated early for this reason are **not** included in the discontinuation/withdrawal group and are considered to have been **fully compliant with treatment**.

---

## 10. Treatment compliance (Treatment compliance)

The clinical trial investigator (or a delegated individual) will encourage and guide participants at every visit when usual care and Chuna manual therapy related to the clinical trial are provided, so that **treatment compliance is maintained**.

Treatment compliance is calculated based on the **number of planned treatment sessions** and the **actual number of sessions received**, using the ratio of the actual number of treatments to the planned number of treatments.

After randomization, treatment compliance is considered adequate when participants have received **at least 5 out of the 8 scheduled Korean medicine treatment sessions**.

To evaluate treatment compliance, the clinical trial investigator (or delegated individual) must keep a **record of the treatments provided**.

Participants whose clinical trial participation is terminated early due to **symptom improvement** according to the early termination criteria are regarded as having been **fully compliant with treatment**.

---

## 11. Rescue medication (Rescue Drug)

From the time of the screening visit, if **intolerable pain** occurs, the use of **certain limited medications** is permitted as rescue medication **at the discretion of the clinical trial investigator**, excluding opioid analgesics and anesthetics.

Specifically, the use of **limited non-steroidal anti-inflammatory drugs (NSAIDs)** and **muscle relaxants** is allowed (medications for protection of the gastrointestinal tract may be co-administered to reduce adverse effects of the rescue drugs).

If rescue medication is taken, the **date of administration and dose** must be recorded in the participant's **diary**.

### ▷ Types of medications that may be used as rescue drugs

- Skeletal muscle relaxants, anticonvulsants, anti-inflammatory analgesics, analgesics, drugs for neuralgia, anticonvulsants, antidepressants,
  - Non-opioid analgesics, antipyretics, weak opioid analgesics, gastrointestinal medications (digestive agents).
- 

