### 2) Exclusion criteria (Exclusion Criteria)

- ① Patients diagnosed with serious specific diseases that can be the cause of low back pain (e.g., spinal metastasis of tumors, acute fracture and spinal dislocation, scoliosis of moderate or greater severity).
- ② Patients with structural abnormalities of the lumbar spine (sacralization, lumbarization), those with a prior history of osteoporosis, or those in whom fracture of the lumbar spine is suspected.
- ③ Patients who are within 3 months after lumbar spine surgery.
- ④ Patients with other chronic diseases that may interfere with the treatment effect or with interpretation of the study results (e.g., chronic renal failure), as judged by the investigator.
- ⑤ Patients with progressive neurological deficits or serious neurological symptoms such as cauda equina syndrome.
- ⑥ Patients who have internal fixation or stabilizing devices in the lumbar spine due to previous lumbar surgery.
- ⑦ Patients with contraindications to interferential current therapy (ICT), such as cancer-related pain or an implanted pacemaker.

- ⑧ Patients who are currently taking systemic steroids, immunosuppressants, psychiatric medications, or other drugs that may affect the study results, as judged by the investigator.
- ⑨ Patients who have received Chuna therapy within the past week, or who have received strong opioid analgesics, anesthetic agents, or invasive treatments such as acupuncture or injection therapy during that period.
- ⑩ Patients who have received nerve block procedures to the lumbar region within the past 2 months.
- ⑪ Patients who are pregnant, breastfeeding, or planning pregnancy during the study period.
- ⑫ Patients who are scheduled, during the 4-week treatment period, to undergo surgery, procedures, or pharmacologic treatment that may affect evaluation of the study results, without this being under the direction of the study physician.
- ⑬ Any other individuals whom the investigator judges to be inappropriate for participation in the clinical trial.
- 

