## 4) Permitted concomitant medications and precautions

In principle, during the clinical trial period, no medications other than the trial interventions provided within this study should be administered. However, because this is designed as a pragmatic clinical trial, **rescue medications** may be administered at the discretion of the principal investigator when they are deemed necessary for the management of adverse events, pain control, and similar clinical needs.

If a concomitantly administered medication is expected to affect the pharmacodynamic evaluation or safety assessment of this trial, the corresponding participant will be withdrawn from the study (for permitted rescue medications, see **Section 13. Rescue medication**).

All concomitant medications and the reasons for their use must be documented in the source documents and the case report form (CRF), and signed by the principal investigator or sub-investigator. For any other medications, participants must be instructed to **consult the study team before taking the medication**.

---

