## 9. Criteria for discontinuation/withdrawal and early termination of the clinical trial

### ○ Criteria for discontinuation/withdrawal

1. The following medications, which are expected to affect the evaluation of the effectiveness of the interventions, **must not be taken from screening until completion of the clinical trial**.

① Strong opioid analgesics; local anesthetics and corticosteroid preparations administered separately from the trial interventions by the attending physician.

- However, based on the clinical judgement of the investigator, non-steroidal anti-inflammatory drugs and muscle relaxants that are prescribed as needed may be used (see 11. Rescue medication).

② Any other drugs that, in the judgement of the clinical trial investigator, may pose a risk to the participant or introduce bias into the evaluation of the study results.

2. Cases in which the participant requests discontinuation of the trial intervention during the clinical trial, or withdraws consent to participate in the study.
3. Cases in which a serious adverse event occurs and the investigator judges that continuation of the trial is not possible.
4. Cases in which major protocol violations such as violation of inclusion/exclusion criteria are newly identified during the clinical trial.
5. Cases in which, although the early termination criteria are not met, the participant does **not attend at least 5 out of the planned 8 treatment sessions**.
6. Any other cases in which it is considered difficult for the participant to continue in the clinical trial, and the principal investigator/sub-investigator judges that the trial should be discontinued for that participant.

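### Section 11 contradicts itself on which rescue drugs are permitted, and the withdrawal clauses elsewhere do not say whether a listed rescue drug is exempt

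*Protocol*

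**What the plan says.** Four places in the Protocol govern medication during the trial.

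- **Section 11, opening text.** Rescue medication for intolerable pain is at the investigator's discretion, "excluding opioid analgesics and anesthetics". The text then narrows this: "Specifically, the use of limited non-steroidal anti-inflammatory drugs (NSAIDs) and muscle relaxants is allowed", with gastrointestinal protection as a permitted addition.
- **Section 11, closing list of drug types.** It names "Skeletal muscle relaxants, anticonvulsants, anti-inflammatory analgesics, analgesics, drugs for neuralgia, anticonvulsants, antidepressants" and continues with "Non-opioid analgesics, antipyretics, weak opioid analgesics, gastrointestinal medications (digestive agents".
- **Section 9, discontinuation/withdrawal, item 1.** The first sub-item prohibits "Strong opioid analgesics; local anesthetics and corticosteroid preparations administered separately from the trial interventions by the attending physician". Its exception is that "non-steroidal anti-inflammatory drugs and muscle relaxants that are prescribed as needed may be used (see 11. Rescue medication". The second sub-item adds any other drug that the investigator judges to put the participant at risk or to bias the evaluation.
- **Section 7, item 4 (permitted concomitant medications).** The principal investigator may give rescue drugs. If a concomitant drug is expected to affect the pharmacodynamic evaluation or the safety assessment, "the corresponding participant will be withdrawn from the study". The same sentence points to section 13 for the permitted rescue drugs.

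Rescue use is also an outcome. Section 14.1 lists it as exploratory, with NSAIDs and muscle relaxants as examples. Section 15, item 2)c, compares the number of uses and the total amount by drug type between the groups.

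**The concern.** The opening text and the list in section 11 are meant to be the same rule, but the list admits a class that the text shuts out. A practitioner who reads the text would refuse a weak opioid. One who reads the list would regard it as permitted.

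The other sections do not settle the matter, and they attach a consequence to it. Sections 7 and 9 both allow withdrawal on a judgement about the drug, and neither says plainly that a drug on the section 11 list is safe from that judgement.

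Rescue medication is given because of pain, and low back pain on the NRS is the primary outcome. The decision lies with investigators who know the allocation (section 7, item 2), at two hospitals. If they apply different parts of the text, analgesic co-treatment and withdrawals may vary for reasons that have nothing to do with the treatments compared. Participants may also receive a drug that another part of the same section excludes.

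**Working it through.** The Protocol gives no figure for rescue use or for withdrawals caused by it, so there is nothing to reproduce. The check is a comparison of the texts by drug class.

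| Drug class | Section 11, opening text | Section 11, list | Section 9, item 1 |
|---|---|---|---|
| NSAIDs, muscle relaxants | allowed, limited | listed | expressly allowed |
| Weak opioids | excluded with all opioids | listed | not named; judgement clause may apply |
| Anticonvulsants, antidepressants, neuralgia drugs | not among the specified drugs | listed | not named; judgement clause may apply |
| Strong opioids | excluded | not listed | expressly prohibited |

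**Step 1: opioids.** The opening text makes no distinction between weak and strong opioids. The list names weak opioids. This is a direct contradiction within one section, so the list cannot be read as a mere elaboration of the text.

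**Step 2: other classes.** The opening text moves from a general permission to a specific one covering two classes plus gastrointestinal protection. The list adds at least three further classes: anticonvulsants (entered twice), antidepressants and drugs for neuralgia.

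**Step 3: the withdrawal clauses.** Section 9 neither prohibits these added classes by name nor includes them in its exception. Whether one of them leads to discontinuation is left to its second sub-item, a judgement. Section 7, item 4, works the same way.

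**Step 4: the cross-reference.** Section 7 refers to section 13 for rescue medication. Section 13 deals with medical care after the trial; rescue medication is section 11. The pointer that might have shown that listed drugs are exempt carries the wrong number.

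**Step 5: route to the primary analysis.** Scheduled NRS assessments are at weeks 0, 4 and 12. Section 8, item 5, places the early discontinuation visit 8 weeks after the last session and ends follow-up there. If the last session falls in week s, with s between 0 and 4, that visit falls in week s + 8, which is week 8 at the earliest. A participant withdrawn before the week-4 assessment may therefore have no week-4 NRS. Section 15 fills missing continuous efficacy values in the FAS by LOCF. The most recent earlier scheduled value is then the baseline, and the imputed change is baseline − baseline = 0.

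**The case against.** The strongest reply is that the express conflict is narrow and that the rest depends on judgement. Much of this stands.

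- A reader might infer that taking a weak opioid or an antidepressant is itself a stated ground for withdrawal. It is not. Section 9 names only strong opioids, local anesthetics and corticosteroids; the other listed classes can lead to withdrawal only through the judgement clauses.
- A reader might infer that section 9 repeats the full opioid exclusion of section 11. It does not: it bars strong opioids only. Its sentence on NSAIDs and muscle relaxants is a permission and does not say that nothing else is allowed.
- A reader might see a further contradiction with exclusion criterion 8, which concerns people "currently taking systemic steroids, immunosuppressants, psychiatric medications, or other drugs that may affect the study results". That is a condition at entry. A trial may exclude current users of a class and still allow the class later as rescue, so this is not a contradiction.
- Section 7 treats permitted rescue drugs as a separate matter and names the rescue section by its title, so the intended target can be guessed despite the wrong number. It still does not say that listed drugs are exempt.
- All concomitant medication is recorded in the CRF whichever rule is followed, and neither the FAS nor the PP definition excludes anyone for rescue use. Allocation is 1:1 in blocks with separate randomization numbers by site, so a difference between sites need not favour one arm.

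These points limit the consequences. They do not remove the contradiction within section 11. The rule must be applied at the bedside, so a statistical analysis plan could not cure it.

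**Conclusion.** The point holds for section 11: its opening text and its list cannot both be followed on weak opioids, and they do not agree on anticonvulsants, antidepressants and neuralgia drugs. It holds as a possible knock-on for sections 7 and 9, whose judgement clauses leave the status of those drugs open, with a wrong cross-reference in section 7.

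The effects on co-treatment, withdrawals and the rescue-use outcome are possible, not certain, and their size cannot be derived from the document. One might be tempted to express the effect as a percentage of the 23 participants per arm. That would only restate the arm size with an assumed count, and section 15 compares the number of uses and total amount by drug type, not the share of participants using rescue. The route to the week-4 NRS rests on two assumptions: that a participant is withdrawn before that assessment, and that no week-4 value is collected.

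**What to change.** Reconcile section 7 (item 4), section 9 (item 1) and both parts of section 11 into one permitted list and one prohibited list. State whether use of a permitted rescue drug is exempt from the withdrawal clauses in sections 7 and 9. Correct the reference in section 7 from section 13 to section 11. Use the same list to define rescue medication in sections 14.1 and 15. Which drugs belong on each list is a clinical decision for the investigators.

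The cost is a short protocol amendment, which section 21 requires the IRB to approve, and matching drug codes in the CRF and participant diary. No extra participants or visits are needed.

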## 12. Criteria for early termination of the clinical trial

If, during the conduct of the clinical trial, a **serious adverse event (SAE)** occurs that may have a serious impact on participant safety or on the progress of the trial:

- The investigator may terminate the participation of the affected participant in the clinical trial at that time.
- If the serious adverse event is considered to be **related to the trial intervention**, **all clinical trial procedures will be suspended**.

Whether the affected participant will continue to participate in the clinical trial after the adverse event will be decided through discussion between the participant and the

research team. If the research team determines, on medical grounds, that the participant can no longer safely continue in the trial, participation may be **forcibly terminated**.

---

### 13. Criteria for medical care and treatment of participants after completion of the clinical trial

If, during or after participation in the clinical trial, a participant experiences **worsening of symptoms related to non-acute low back pain** or **adverse effects** and requests related treatment, appropriate medical care will be provided in accordance with the hospital's standard guidelines.

If a participant requires treatment, all medical costs will be covered according to the terms of the **clinical trial insurance contract**.

Participants whose clinical trial participation has been completed may receive medical care at any time, under the direction of the attending physician, in preparation for the occurrence of unexpected **delayed adverse reactions**.

If an adverse event occurs during the clinical trial, the trial site will provide **appropriate medical management** until the participant has recovered, and the research team will decide, through discussion, whether the participant can continue to take part in the trial.

---

### 14. Efficacy and safety evaluation

#### 14.1 Efficacy evaluation

##### ☐ Primary efficacy outcome

- The **primary efficacy outcome** of this clinical trial is the **change in low back pain intensity** measured by the **Numeric Rating Scale (NRS)**.
- NRS for low back pain is assessed at **baseline (week 0)**, **end of treatment (week 4)**, and **follow-up (week 12)**, and the change from baseline at each time point is compared between the two groups.

##### ☐ Secondary efficacy outcomes

###### ① NRS for leg pain (radiating pain)

- Patients rate the intensity of radiating pain to the lower limb on an 11-point numeric rating scale (0–10), similarly to low back pain NRS.

- At baseline, week 4, and week 12, the following questionnaires are administered:

#### ② Oswestry Disability Index (ODI)

- A standardized questionnaire that evaluates the degree of disability caused by low back pain in daily activities (such as personal care, lifting, walking, sitting, standing, sleeping, social life, and traveling).
- The total score is calculated according to the validated scoring method, and the degree of functional impairment is expressed as a percentage.

#### ③ European Quality of Life 5 Dimension (EQ-5D-5L)

- A generic health-related quality-of-life instrument with 5 dimensions (mobility, self-care, usual activities, pain/discomfort, anxiety/depression), each with 5 levels of severity.
- In this trial, the EQ-5D-5L index score is calculated using the Korean valuation set and used as a secondary outcome.

#### ④ Roland-Morris Disability Questionnaire (RMDQ)

- A questionnaire that assesses the impact of low back pain on daily activities and functional status.
- The total score is calculated from the number of items checked, and higher scores indicate greater disability.

### 2. Physical examination – Lumbar range of motion (ROM)

- To evaluate changes in lumbar mobility, **lumbar ROM** is measured at baseline, week 4, and week 12, including:
  - Flexion,
  - Extension,
  - Lateral flexion (right and left),
  - Rotation (right and left).
- Measurements are performed using a standardized method (e.g., inclinometer or goniometer) according to the study site's SOP, and the degrees are recorded.

### 3. Imaging evaluation

- At baseline (screening radiographs), week 4, and week 12, **L-spine AP and lateral standing radiographs** are obtained according to the standardized imaging protocol.
- Using a DICOM labeling program developed by the Korea Institute of Oriental Medicine, the following are calculated for each lumbar vertebral level:

- Relative angles for **flexion, extension, lateral bending, and rotation**,
- **Chuna malposition diagnosis results** based on the predefined cut-off values.
- These imaging parameters are used as secondary or exploratory outcomes to investigate changes in spinal alignment and their association with clinical improvement.

#### 4. Exploratory efficacy outcomes

- From the end of the 4-week treatment period until the 12-week follow-up, the following are investigated and compared between groups as exploratory outcomes:
  - ① Whether additional **invasive procedures** for low back pain were performed
    - e.g., injection therapy such as **nerve blocks, radiofrequency ablation, or lumbar surgery**.
  - ② Whether **strong opioid analgesics** were used for pain control.
  - ③ **Rate of early termination of treatment** due to sufficient symptom improvement (based on the early-termination criteria).
  - ④ **Use of rescue medications**
    - Type, dose, and frequency of rescue medications (NSAIDs, muscle relaxants, etc.) are recorded and analyzed.

#### 5. Classification of responders and non-responders

- Using the change in NRS from baseline, the **minimal clinically important difference (MCID)** for low back pain is defined as a **decrease of 2 points or more** on the NRS.
  - ① Participants with a reduction of  **$\geq 2$  points** on the NRS from baseline to each time point (weeks 4 and 12) are classified as the **treatment responder group**, and those with  **$< 2$ -point reduction** are classified as the **non-responder group**.
  - ② In addition, participants whose trial participation is **terminated early due to symptom improvement** in accordance with the early-termination criteria are also classified as belonging to the **responder group**.

### 14.2 Safety evaluation

- (1) **Physical examination and vital signs:** Performed at every visit after randomization

- The results of the physical examination and vital signs are reviewed comprehensively, and whether each test is normal or abnormal is determined for each individual participant.

**(2) Confirmation of adverse events such as subjective and objective symptoms:**

Performed at every visit after randomization

- The clinical trial investigator must record all adverse events and concomitant medications that occur during the trial.
- Adverse events and concomitant medications are recorded in the case report form (CRF). For adverse events, the following must be documented: the symptoms and signs of the event, duration (start date/end date), severity, outcome, seriousness, causal relationship with the investigational intervention, and any actions taken in relation to the adverse event.
- Symptoms or signs that were already present before participation in the clinical trial are not recorded as adverse events. However, if after enrollment there is any change in the frequency, severity, or extent of such symptoms or signs, they must be recorded as adverse events.
- For concomitant medications, the generic name, dose, period of administration, and reason for use must be recorded in detail (for specific evaluation methods, see **Section 18. Methods for reporting and evaluating adverse events**).

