## 3) Treatment visits (Visits 3–10; both groups)

(1) Chuna + usual care group (Group I; Visits 3–10)

- Starting immediately after the baseline visit, participants receive treatment **twice per week for 4 weeks**, for a total of **8 sessions** according to the allocated intervention (usual care + Chuna).

(2) Usual care-only group (Group II; Visits 3–10)

- Starting immediately after the baseline visit, participants receive **usual care only** twice per week for 4 weeks (8 sessions).

(3) Assessments at each treatment visit (both groups)

- Before treatment at each visit, the following items are checked:
  - Occurrence of adverse events since the previous visit.
  - Vital signs: sitting blood pressure, pulse rate, body temperature (measured after at least 5 minutes in the sitting position without abrupt postural changes).

---

**4) Assessment visits** (same for Groups I and II – Visits 2, 10, and 11)

(1) All participants who pass screening will visit the outpatient clinic at baseline, at the end of the treatment period (4 weeks after baseline), and 8 weeks after completion of all treatments (12 weeks after baseline) to undergo the following assessments.

(2) Vital signs

(3) Assessment of subjective symptoms and function

- Primary and secondary efficacy outcomes are assessed using questionnaires on pain intensity and function: NRS, ODI, EQ-5D-5L, and RMDQ.

(4) Physical examination

- Lumbar range of motion (ROM):  
Flexion, extension, lateral flexion (right and left), rotation (right and left).

(5) Imaging evaluation

- Standardized lumbar spine AP and lateral standing radiographs (L-spine AP & lateral standing view) are obtained.
- Based on the acquired images, vertebral-level relative angles (flexion, extension, lateral bending, rotation) and Chuna malposition diagnosis results are derived using a DICOM labeling program and compared across time points.

(Note: No separate imaging assessment is performed at Visit 2; the imaging evaluation at Visit 2 is replaced by the screening radiographs obtained at Visit 1.)

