### 3) Safety analysis

- For adverse events, the **number of events**, **number of affected participants**, **severity**, and **causal relationship with the intervention** will be summarized descriptively by treatment group. If necessary, **nonparametric methods** may be applied.
  - Vital signs, physical examination findings, and patients' subjective complaints will be comprehensively reviewed. For any parameters judged by the investigator to show **clinically meaningful changes**, statistical analyses may be performed as needed.
  - For continuous data, the **number of observations**, **mean**, **standard deviation**, **median**, **minimum**, and **maximum** will be presented by visit. Within-group changes will be analyzed using a **paired t-test** or **Wilcoxon signed-rank test**.
  - For adverse event data, between-group comparisons will be conducted using the **Chi-square test** or **Fisher's exact test**.
  - If clinically meaningful changes are observed and a comparison between groups is needed, methods such as **generalized estimating equations (GEE)** may be used to evaluate whether there are statistically significant differences between groups over time.
- 

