## 16. Methods for reporting and evaluating adverse events

Following Chuna manual therapy, the expected adverse reactions include **worsening of pain at the treatment site**, **fatigue**, etc., and in rare cases **nerve injury** and **fracture** may occur. For ICT, possible adverse reactions include **skin irritation** at the treatment site, **burns**, **blistering**, and **discomfort after treatment**.

In this study, the scope of adverse events related to the study procedures is defined on this basis as follows:

- For **Chuna manual therapy**, adverse events include **worsening of pain**, **fatigue**, **fracture**, and **nerve injury**.
- For the **usual care group (ICT)**, adverse events include **burns**, **blistering**, and **worsening of pain**.

Adverse events that are clearly **unrelated to the study interventions** are **not** classified as serious adverse events for the purpose of this protocol. The methods for reporting and evaluating adverse events are described below and are adapted from the

standard procedures used in drug–intervention clinical trials, applying the same basic definitions and evaluation criteria.

The investigator must record **all adverse events** that occur during the clinical trial. In the case report form (CRF), the following must be documented for each adverse event:

- Symptoms and signs,
  - Duration (start date / end date),
  - Severity,
  - Course and outcome,
  - Seriousness,
  - Causal relationship to the clinical trial procedure,
  - Actions taken in relation to the adverse event.
- 

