## 1) Definitions

### (1) Adverse Event (AE)

An adverse event is any unfavorable and unintended sign, symptom, or disease that occurs in a participant who has received a clinical trial procedure, and **does not necessarily have a causal relationship** with that procedure.

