## 2) Evaluation of adverse events

- In this clinical trial, adverse events include any undesirable and unintended signs or symptoms that were **not present before the start of the trial** and that newly appear during the treatment period, regardless of whether a causal relationship to the clinical trial procedure is established.
- All events that are expected adverse reactions to the clinical trial procedure (symptoms and signs, onset date, duration, etc.) must be fully and accurately recorded in the adverse event section of the CRF.
- The **severity** of adverse events will be graded by the principal investigator and sub-investigators according to a stepwise scale, with reference to **"4) Assessment of the relationship to the clinical trial procedure."**
- The **causal relationship** between the clinical trial procedure and the adverse event will be classified into **six categories** as described in **"4) Assessment of the relationship to the clinical trial procedure."**

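### Section 14.2 records change in a pre-existing symptom as an adverse event without saying that the change must be a worsening, and conflicts with the adverse-event rules in Section 16

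*Protocol*

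**What the plan says.** Section 14.2, item (2), starts from a general exclusion: "Symptoms or signs that were already present before participation in the clinical trial are not recorded as adverse events". It then makes an exception, which is mandatory: if after enrolment there is "any change in the frequency, severity, or extent of such symptoms or signs, they must be recorded as adverse events". The exception does not say in which direction the symptom must change.

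Section 16 treats the same matter in three places:

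- Its opening text lists the harms attributed to each treatment. For Chuna manual therapy, "adverse events include worsening of pain, fatigue, fracture, and nerve injury". Worsening of pain is also listed for the usual care group.
- Under 1) Definitions, item (1): "An adverse event is any unfavorable and unintended sign, symptom, or disease that occurs in a participant who has received a clinical trial procedure".
- Under 2) Evaluation of adverse events, events are described as undesirable signs or symptoms that were absent before the trial began and "that newly appear during the treatment period, regardless of whether a causal relationship to the clinical trial procedure is established".

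At each treatment visit (Section 8, 3)) staff check "Occurrence of adverse events since the previous visit". Section 15, 3) then states: "For adverse event data, between-group comparisons will be conducted using the" chi-square or Fisher's exact test.

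**The concern.** Section 6, 1) admits only patients with low back pain rated 4 or more on the numeric rating scale (NRS). Low back pain is therefore a pre-existing symptom in all 46 participants, and its change is the primary outcome (Section 14.1). A rule that makes every change in a pre-existing symptom an adverse event covers the effect the trial is designed to produce.

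If staff apply Section 14.2 as worded, a participant whose pain falls must be recorded as having an adverse event. If they apply the evaluation rule in Section 16, 2) as worded, a participant whose pain worsens need not be, because the pain was there before. The definition and the list of expected reactions lie between the two. At stake is the between-group comparison of adverse events: which events enter it depends on which sentence the site follows, and two sites recruit.

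**Working it through.** **Reproducing the plan's figures.** The only relevant figures are the planning values in Section 6, 3): NRS reduction 3.02 (SD 1.72) with Chuna plus usual care and 1.36 (SD 1.75) with usual care.

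- Pooled SD = √[(1.72² + 1.75²)/2] = 1.735, so d = (3.02 − 1.36)/1.735 = 0.957, which agrees with the stated 0.96.
- n = 2 × (1.96 + 0.84)²/0.96² = 17.01, rounded up to 18.
- 18/0.80 = 22.5, rounded up to 23 per group and 46 in total.

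These reproduce. The protocol states no expected adverse-event rate, so there is no such figure to check.

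**The sentences side by side, applied to low back pain.**

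| Place | Pain falls | Pain worsens |
|---|---|---|
| Section 14.2, item (2) | event | event |
| Section 16, 1), item (1) | not an event (not unfavourable) | event |
| Section 16, opening list | not named | event |
| Section 16, 2) | not an event | not described (symptom already present) |

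**Size of the difference.** Assumptions: the planning values describe the change at week 4, reductions are normally distributed, and scores are whole points, so a change of at least one point is a reduction beyond ±0.5. With mean reduction m, SD s and threshold c:

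- P(any change) = 1 − [Φ((c − m)/s) − Φ((−c − m)/s)]
- P(worse) = Φ((−c − m)/s)

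At c = 0.5:

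- Chuna: Φ(−1.465) = 0.071 and Φ(−2.047) = 0.020, so any change = 1 − (0.071 − 0.020) = 0.949 and worse = 0.020.
- Usual care: Φ(−0.491) = 0.312 and Φ(−1.063) = 0.144, so any change = 1 − (0.312 − 0.144) = 0.832 and worse = 0.144.

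Multiplied by 23 per arm, this is 21.8 against 19.1 participants with any change, and 0.5 against 3.3 with worsening. Section 16, 2), taken as the whole rule, would give none in either arm.

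The protocol sets no threshold for a change, so c was varied. The last column is the exact probability that a two-sided Fisher test on the any-change counts gives p < 0.05 with 23 per arm.

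| c (NRS points) | Any change, Chuna vs usual care | Worse, Chuna vs usual care | Fisher p < 0.05, any change |
|---|---|---|---|
| 0.5 | 94.9% vs 83.2% | 2.0% vs 14.4% | 13.2% |
| 1.0 | 89.0% vs 67.0% | 1.0% vs 8.9% | 33.5% |
| 1.5 | 81.6% vs 51.9% | 0.4% vs 5.1% | 46.5% |
| 2.0 | 72.5% vs 38.5% | 0.2% vs 2.7% | 55.1% |

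With 18 per arm the last column runs from 7.5% to 45.6%. At every threshold the Chuna arm has more events under the literal reading and fewer under the worsening reading.

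**The case against.** The strongest reply is that nobody reading the whole protocol would log less pain as harm. The formal definition requires an unfavourable event and the evaluation rule an undesirable one. The expected reactions name worsening. Improvement is treated elsewhere as response or as grounds for successful early completion (Sections 9 and 14.1). The severity grades in Section 16, 3) describe tolerability and interference with daily activity, and cannot sensibly be completed for a reduction in pain. This largely stands: a reader might infer that improvement is certain to be counted as harm, and the documents do not support that. What remains is that Section 14.2 is the operative recording instruction, is mandatory, and contradicts the definition it should apply.

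A reader might also infer that, because events are asked about since the last visit, partial rebounds after improvement must count, and that the more effective arm would have more of them. The documents do not support this either. The phrase in Section 8 sets the interval for asking, not the level against which severity is judged. The protocol gives no visit-to-visit variability, so rebound rates cannot be derived from it, and nothing in it shows an excess in one arm.

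Two lesser points carry some weight. Section 15, 3) also summarises events by severity and causal relationship, which would help a reader of the results separate treatment reactions from fluctuation; it does not settle which events enter the test. And Section 16, 2) says that events *include* new symptoms, so it may not be meant as exhaustive. That softens the conflict with Section 14.2 but leaves the rule unstated.

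**Conclusion.** The point holds as a wording defect and an internal inconsistency. Section 14.2 omits the direction of change for a symptom that every participant has, and Sections 14.2 and 16 do not give one rule. Distortion of the safety comparison is a risk that depends on how sites read the text.

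The possible size is not trivial. For back pain alone at week 4, about 95% against 83% of participants would be events under the literal reading, and about 2% against 14% under worsening only, so the reading can reverse the order of the arms. These figures rest on the planning means and SDs, on normality, on week 4 as the time of measurement, and on ignoring all other adverse events. They are a snapshot: counting over all visits can only raise the shares with at least one event, and could narrow the gap between arms.

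**What to change.** In Section 14.2, item (2), replace *any change* by *any worsening*. Then bring Section 14.2 and the three places in Section 16 (opening list, definition, evaluation rule) into one rule: a new unfavourable symptom is an event, and so is worsening of a symptom present at entry. In the between-group comparison in Section 15, 3), show worsening of the study condition (low back or leg pain) in its own row.

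Do not make worsening beyond the entry level a condition. NRS is collected only at Visits 2, 10 and 11, and the treatment-visit checks in Section 8, 3) list only adverse events and vital signs. A flare after a session that stayed below the entry score would drop out of adverse-event capture and usually leave no trace in the NRS data, although worsening of pain is an expected reaction to Chuna.

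The cost is one word in Section 14.2, an aligned sentence in Section 16, one table row, and the same instruction to staff at both sites. Some ordinary fluctuation in pain will still be recorded as events; the separate row and the causality assessment keep it visible as such. The row is a display matter that the statistical analysis plan, not shown here, could carry; the wording of the recording rule belongs in the protocol.
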